### Second Part: Prospective Cohort Study

The cohort study will collect data on the ovarian reserve and sperm from patients undergoing gonadotoxic therapies. Data collection was initiated on December 1, 2023, and will be continued at least for 5 years to analyze short-term fertility. Long-term fertility data will be collected until at least 2036. An initial version of the FertiTOX internet-based platform is expected to be set up in 2026. The trial is registered in ClinicalTrials.gov (NCT05885048).

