### Inclusion Criteria

Each center that counsels patients with cancer about fertility issues and can also provide fertility-associated parameters may participate. A prerequisite requirement is that each center has received ethical approval for the study. Even though the study is intended to mainly include FertiPROTEKT network centers [14] and FERTISAVE [15] networks in Germany, Switzerland, and Austria, any other center worldwide can participate if the inclusion criteria are fulfilled.

Women and men aged 14-50 years (18-50 years in Germany due to national regulations) undergoing cancer therapies using chemotherapy, radiotherapy, or immune therapy (Figure 1) will be included.

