### Recruitment and Informed Consent Procedure

Patients are recruited by reproductive physicians who are associated with the participating infertility centers. Approximately 70 centers (44 in Germany, 21 in Switzerland, and 6 in Austria) will participate in the study and will collect data (see Multimedia Appendix 1).

Patients who need gonadotoxic therapies will be counseled before the onset of the respective therapies. During counseling, patients are screened for their eligibility to be included in the study.

Furthermore, patients will be provided counseling forms to provide informed consent before the onset of gonadotoxic therapy to collect specific basic data and data on gonadal function from patients with cancer. Data will also be collected 12-15 months and 5 and 10 years after the end of gonadotoxic therapy.

The study participants will be informed that they will be contacted by the fertility center or a defined coworker of the study by telephone, email, or post to collect the respective data after the administration of gonadotoxic therapy.

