### Sample Size Calculation

A power calculation was performed to determine whether the expected number of patients is sufficient to detect an effect of cancer treatment on fertility with a reasonable power.

The calculation was performed for the primary outcome (ie, sperm count for men and AMH concentration for women) for men and women separately. Calculations were performed within each cancer entity and for each specific treatment protocol separately with a paired *t* test using Stata (release 17.0; StataCorp).

We set the effect size so that a relative risk of 50% was not missed. For the sperm count, where the mean value in healthy men is 64 million (SD 47 million) [17], this would correspond to an effect size of 0.67. For AMH concentration in women, where means and SDs can be assumed to be equal [18], it would correspond to an effect size of 0.5. The intraindividual correlation was set to 0.5 [17,18]. To account for multiple testing (analysis will be performed with 43 treatment groups for men and women separately), the Šidák correction was used, and the significance level was adjusted to 0.0006 (2-sided).

Table 1 shows that a sufficient power of >80% will be reached for most treatments. If the number of cases was twice as high and the intrapatient correlation coefficient was 0.7, a power of >80% would be reached for all treatment levels. As the study is expected to be extended, a sufficient number of patients can be expected in order to reach this goal.

**Table 1 table1:** Expected number of cases and resulting power reached per specific treatment (treatment protocols) in the most common *ICD (International Classification of Diseases)* cancer groups [19].

*ICD* cancer group	Cases, n^a^	Specific treatments (treatment protocols), n	Effect size (females/ males)^b^	Power (females/ males)^b^, %/%
Breast	2000	6	0.5/—^c^	100/—
Hodgkin lymphoma	1000	2	0.5/0.68	100/100
Bone and articular cartilage	400	3	0.5/0.68	98.6/100
Female genital organs	350	3	0.5/—	96.5/—
Male genital organs	2000	4	—/0.68	—/100
Digestive organs	200	7	0.5/0.68	14.3/41.4
Mesothelial and soft tissue	200	3	0.5/0.68	67.2/96.7
Eye, brain, and central nervous system	300	2	0.5/0.68	99.5/100
Non-Hodgkin lymphoma	300	8	0.5/0.68	26.2/64.4
Leukemia	200	5	0.5/0.68	30.6/70.8

^a^The estimation of the number of cases is based on the number of patients previously counseled and documented in the FertiPROTEKT and FERTISAVE registries.

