### Data Analysis

The impact of cancer therapies and chemotherapies on the primary outcomes will be assessed for each *ICD* cancer group [19] and for each specific treatment regimen separately by comparing values measured before and after the gonadotoxic therapy using paired *t* tests. *P* values will be adjusted for multiple testing using the false discovery rate controlling procedure.

Consequences on other fertility parameters measured before and 12-15 months after the end of gonadotoxic therapy (ie, AMH, FSH, LH, and E2 concentrations in women and total testosterone, FSH, and LH concentrations and total sperm count, sperm concentration and motility in men) will be assessed using the same methodology, but without false discovery rate adjustment. Long-term consequences will be investigated later by comparing values measured before and 5 and 10 years after the gonadotoxic therapy. However, due to the long period until the final analysis, statistics might be adapted in relation to future development of cancer and fertility-preserving therapies.

As age was identified to potentially modify the effect of gonadotoxic therapy on female fertility, we will additionally conduct stratified analyses and document the impact of gonadotoxic therapy in the different female age groups.

Finally, the effects of different cancers, treatment protocols, age, and the presence of the patients’ children before cancer therapy on primary and secondary fertility outcomes will be analyzed using linear mixed effect models.

The frequency of patients undergoing fertility-preserving treatments, namely freezing of ovarian tissue, oocytes and embryos, testicular tissue, and sperm will be calculated for each *ICD* cancer group and for each specific treatment protocol separately and additionally presented with the associated 95% Wilson CI. Potential effects of the patients’ characteristics on the abovementioned binary outcomes will be analyzed using logistic regression analysis.

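### The 5- and 10-year AMH comparison has no age reference, so expected ovarian ageing is counted as an effect of therapy

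*Protocol article*

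**What the plan says.** The primary objective (Objectives) is whether cancer therapies and specific chemotherapy protocols lower AMH in women. The cohort is made up of treated patients: "The cohort study will collect data on the ovarian reserve and sperm from patients undergoing gonadotoxic therapies". Eligibility is set as "Women and men aged 14-50 years (18-50 years in Germany due to national regulations) undergoing cancer therapies".

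Under Data Analysis, impact on the primary outcomes is assessed "by comparing values measured before and after the gonadotoxic therapy using paired *t* tests", per cancer group and per regimen. For the later visits the text says: "Long-term consequences will be investigated later by comparing values measured before and 5 and 10 years after the gonadotoxic therapy". It adds that the statistics may be adapted, and gives future developments in cancer and fertility-preserving therapies as the reason.

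Visits are timed from the end of treatment: "Data will also be collected 12-15 months and 5 and 10 years after the end of gonadotoxic therapy". The interval from baseline is therefore longer than the nominal follow-up by the duration of therapy.

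Age appears twice in Data Analysis. It is first a possible modifier of the therapy effect: "we will additionally conduct stratified analyses and document the impact of gonadotoxic therapy in the different female age groups". It is then one of several terms, with cancer, protocol and existing children, in linear mixed models for the primary and secondary outcomes. The Limitations section does not mention ageing.

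**The concern.** AMH is expected to fall with age in women who receive no gonadotoxic therapy. A within-woman comparison with baseline takes zero change as its null. Over five or ten years that null is wrong even for a harmless regimen, because the measured change is the sum of ageing and therapy. A woman over 40 at entry is over 50 at the 10-year visit, and one enrolled at 50 is about 60.

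The results are meant for a public platform used to counsel patients on fertility preservation, and the Introduction itself names overtreatment as a risk. Attributing ageing to therapy overstates gonadotoxicity and so pushes in that direction.

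**Working it through.** **Inputs from the article (Sample Size Calculation and Table 1).** AMH mean equals SD; design effect is a 50% fall, so d = 0.5; within-patient correlation 0.5; two-sided level 0.0006, a Šidák correction that matches 43 groups in each sex: 1 − 0.95^(1/86) = 0.000596. The number per protocol is cases divided by protocols. I use two female-only groups, where no sex split is needed: breast 2000/6 = 333 and female genital organs 350/3 = 116.

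**Inputs assumed.** Annual age-related AMH decline r of 2, 5, 8 or 10% (none is given). Treatment time of about half a year (none is given), so the intervals from baseline are t = 1.5, 5.5 and 10.5 years, taking the first visit at about 12 months. No attrition. The same paired t test and the 0.0006 level are applied at the long-term visits, for which the article names neither test nor level.

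**Step 1: reproduce the plan's figure.** SD of the difference = SD × √(2(1 − 0.5)) = SD. Exact paired-t power (noncentral t) at d = 0.5 and level 0.0006 gives 96.5% for n = 116, as in Table 1 for female genital organs. For n = 133 it gives 98.6%, as in Table 1 for bone.

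**Step 2: fall from ageing alone.** With no toxicity the proportional fall is 1 − (1 − r)^t. For example, 1 − 0.95^5.5 = 0.246. Because mean = SD = SD of the difference, this fall is also the standardised effect d.

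| Assumed decline per year | 1.5 years | 5.5 years | 10.5 years |
|---|---|---|---|
| 2% | 3.0% | 10.5% | 19.1% |
| 5% | 7.4% | 24.6% | 41.6% |
| 8% | 11.8% | 36.8% | 58.3% |
| 10% | 14.6% | 44.0% | 66.9% |

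As a share of the 50% target, this is 6-29% at 1.5 years, 21-88% at 5.5 years and 38-134% at 10.5 years.

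**Step 3: probability that a non-toxic protocol is declared significant.** The noncentrality is d√n. For 5% per year at 5.5 years with n = 333 it is 0.246 × √333 = 4.49, against a critical value of 3.46, which gives 84.5%.

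| Assumed decline per year | n = 333: 1.5 y | n = 333: 5.5 y | n = 333: 10.5 y | n = 116: 5.5 y | n = 116: 10.5 y |
|---|---|---|---|---|---|
| 2% | 0.2% | 6.3% | 51.0% | 1.0% | 7.7% |
| 5% | 1.8% | 84.5% | about 100% | 19.7% | 82.6% |
| 8% | 9.6% | 99.9% | about 100% | 66.6% | 99.6% |
| 10% | 21.5% | about 100% | about 100% | 88.2% | about 100% |

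The nominal rate is 0.06%.

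**Step 4: the pooled breast group at 1.5 years.** With all 2000 women paired, the same calculation gives 1.8%, 45%, 97% and 99.9% for 2, 5, 8 and 10% per year. The short-term analysis is therefore exposed mainly in this pooled group.

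**Step 5: do the planned age analyses remove it?** Stratification shows how the total change differs between age groups, but the change within each stratum still contains that stratum's ageing. A mixed model could separate the two if age were attained age at each visit, because pre-treatment AMH across ages would then supply an internal reference. The article says only that age is a term. It does not say which age, and it ties the models to the primary and secondary outcomes, while End Points lists the 5- and 10-year values separately.

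**The case against.** The strongest reply has four parts.

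- **The primary analysis is at 12-15 months, and the long-term method is deferred and open to adaptation.** The first half stands as a limit on scope: a 3-15% fall is modest against a 50% target. The second half does not answer the point. The stated reason for adaptation is new therapies, and the one comparison that the article names is the raw one.
- **The figures rest on a decline that the documents do not give.** This stands. A reader might infer that any harmless therapy will show a significant long-term reduction. At 2% per year and n = 333, the probability at 5.5 years is only 6%. Attrition, which the Discussion expects, would lower the rejection rates, but not the bias in the estimate. The 0.0006 level comes from the power calculation, whereas the primary outcomes are to be adjusted by false discovery rate, so these are not the plan's actual rejection rates.
- **A reader might infer that the bias is largest in older women.** The documents do not support this. The calculation applies one proportional rate at every age, and on the concentration scale that gives a larger absolute fall where baseline AMH is higher.
- **Age is already in the mixed models alongside protocol.** This partly stands. The models address age differences between protocols, so it would be too strong to say that protocol comparisons are necessarily distorted or that age adjustment cannot help. As described, they do not remove the ageing change shared by all protocols, and the stated assessment of impact is still the before-after comparison.

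**Conclusion.** The point holds for the 5- and 10-year AMH comparisons. As written, they attribute expected ovarian ageing to therapy. This comes from the comparison that the article names, not from detail left to an analysis plan. Under an assumed 2-10% annual decline, ageing alone accounts for a fall of about 10-44% at 5.5 years and 19-67% at 10.5 years. For a protocol with 333 women and no toxicity, the chance of a significant result is 6% to about 100%, and 51% to about 100%, respectively. These figures also rest on mean = SD, correlation 0.5 over the whole interval, level 0.0006, about half a year of treatment and no attrition.

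A reader might go further and call the primary analysis unsound. The figures do not support that. At 1.5 years a single protocol of 333 rejects in 0.2-21.5% of cases, and the bias matters mainly for the pooled breast group and for the reported effect size. For an exploratory cohort whose long-term data run to at least 2036, this should be fixed before those data are analysed. It does not undermine the study as a whole.

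**What to change.** For the 5- and 10-year ovarian comparisons:

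- Make the inferential estimate the change in excess of age-expected AMH. Obtain it from a linear mixed model with attained age at each visit, using the cohort's own pre-treatment AMH across ages as the internal reference.
- Add a sensitivity analysis with AMH age-standardised to a published reference curve.
- Report results by attained age, and show women beyond a pre-stated attained age separately. Enrolment stops at 50, so the internal reference has no pre-treatment values above that age.
- Show raw change from baseline descriptively only.

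At 12-15 months, keep the paired test and report the age-expected change beside it.

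**Cost.** Some extra modelling and a few sentences of analysis text. No new data are needed, because year of birth is already recorded (Ethical Considerations). The internal reference assumes that the difference in pre-treatment AMH between women of different ages mirrors ageing within a woman. The external curve depends on assay and reference population, which matters with about 70 centres contributing, and for that reason it should be the sensitivity analysis.

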### Objectives

The primary objective is to determine whether cancer therapies and specific chemotherapy protocols reduce AMH concentrations in women and sperm quality in men.

Secondary objectives are to analyze the impact of cancer therapies and chemotherapies on other fertility parameters such as the probability of undergoing fertility-preserving treatments in relation to the type of cancer disease and specific treatment protocols, the number of children, the future wish to have children, and age. Further objectives are to assess satisfaction with the decision to have undergone fertility-preserving procedures, the proportion of women and men who use their frozen gametes to achieve a pregnancy, the effect of different gonadotoxic therapies on long-term fertility, and the quality of life after the administration of cancer therapies. 

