### End Points

The primary end points are the AMH concentration in women and sperm count before and after gonadotoxic treatments. End points will be assessed before and 12-15 months after the end of the gonadotoxic treatments (patients with melanoma receiving adjuvant checkpoint inhibitor treatment will be evaluated every 3 months).

Secondary end points are FSH, LH, and E2 concentrations in women and total testosterone, FSH, and LH concentrations, total sperm count, and sperm motility in men. Further secondary outcome parameters are the number of patients who freeze gametes and gonadal tissue and satisfaction with the decision to have undergone fertility-preserving measures.

Long-term end points to be determined 5 and 10 years after the end of the gonadotoxic therapy are the abovementioned hormone and sperm parameters as well as the number of patients who become pregnant after gonadotoxic therapies spontaneously or after the use of frozen gametes and gonadal tissue.

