To bridge this data gap, we designed a study to analyze published data and data that will be collected in at least 3 countries by centers belonging to the FertiPROTEKT network. The data will be analyzed und disseminated via the FertiFOX web-based platform to provide patients, researchers, and clinicians access to the analysis, which will be graphically illustrated. By including patients’ representatives in the data analysis, we will ensure that the data are presented in a manner that is also understandable to patients. The data will not only be presented as a single curve presenting the means and showing odds ratios and CIs, which presents the average impact of therapies on gonadal function, but also show individual variations by presenting a set of curves.

The study has been designed to follow up on patients for at least 10 years. Such a long follow-up will enable us to evaluate how many patients have undergone fertility-preserving procedures but unfortunately did not survive. Furthermore, we will be able to estimate how many patients conceived spontaneously or by using the frozen gametes and gonadal tissue. Such an analysis is essential to evaluate the long-term efficacy of fertility preservation counseling and treatment. We are aware that some patients might be lost to follow-up. However, as the number of included patients is expected to be very high, it can be assumed that the amount of data will still be sufficiently high.

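### The long-term analysis compares 5- and 10-year values only with baseline and leaves out the 12-15 month value, so selective return can bias the long-term change

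*Protocol article*

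**What the plan says.** **Measurements.** Under Recruitment and Informed Consent Procedure, after the pre-therapy data, "Data will also be collected 12-15 months and 5 and 10 years after the end of gonadotoxic therapy". End Points fixes what is measured late: "Long-term end points to be determined 5 and 10 years after the end of the gonadotoxic therapy are the abovementioned hormone and sperm parameters", together with pregnancies. The same parameters are therefore available at four time points.

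**Long-term analysis.** Data Analysis gives one comparison: "Long-term consequences will be investigated later by comparing values measured before and 5 and 10 years after the gonadotoxic therapy". The next sentence keeps the method open: "However, due to the long period until the final analysis, statistics might be adapted in relation to future development of cancer and fertility-preserving therapies".

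**Other analyses that might bear on it.** Data Analysis also says that the effects of cancer type, protocol, age and existing children "on primary and secondary fertility outcomes will be analyzed using linear mixed effect models". Time since therapy is not among the listed effects, and the visits that enter are not specified.

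**Objective and attrition.** The long-term objective is "the effect of different gonadotoxic therapies on long-term fertility". Anticipated Findings concedes "We are aware that some patients might be lost to follow-up" and replies that the expected number of patients is large enough. It also describes the platform display: "The data will not only be presented as a single curve presenting the means and showing odds ratios and CIs", with a set of individual curves alongside.

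**The concern.** The 12-15 month value is the best available predictor of who returns later and of what the missing late value would have been. A comparison of baseline with 5 years does not use it. If the paired method of the short-term analysis is carried over, a patient without a 5-year value contributes nothing to the 5-year result, even when her or his 12-15 month value is known.

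Patients are recontacted by fertility centers or study staff over a decade, so return may well be related to gonadal function. Those with preserved function may come back more often, or those with failure may come back to use frozen material. A large sample makes the estimate precise but does not remove this bias.

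At stake is what a patient is told. The long-term result answers a stated objective and goes to a public counseling platform. Readers will set the 1-, 5- and 10-year results side by side and infer recovery or lasting loss, although the plan names no contrast that addresses this.

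**Working it through.** **The plan's own figure.** The article has no calculation for the long-term comparison. Its only design calculation is Table 1, for the paired pre/post test. A two-sided paired *t* test at 0.0006 with correlation 0.5 and n = 200/3, rounded down to 66 (mesothelial and soft tissue), gives 67.2% power at effect size 0.5 and 96.7% at 0.68. Both agree with the table. Only the effect size of 0.5 and the correlation of 0.5 are carried into the illustration below.

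**Inputs**
- From Sample Size Calculation: a change of 0.5 SD (women, AMH) and a within-patient correlation of 0.5, used here for baseline with each later value.
- Assumed, not in the article: correlation 0.8 between 12-15 months and 5 years; return at 5 years of 80%, 60% or 40%; odds ratio of return of 1, 1.5, 2 or 3 per SD of the 12-15 month value; all patients measured at baseline and 12-15 months.
- Truth set in the illustration: mean change from baseline of -0.5 SD at 12-15 months and -0.5 SD at 5 years, so no true change between them.

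**Formula.** Let all values have unit SD and be jointly normal, and let return depend only on the 12-15 month value. Let *s* be the amount by which the mean 12-15 month value of returners exceeds that of all patients. The returners' mean is then shifted by 0.5*s* at baseline, by *s* at 12-15 months and by 0.8*s* at 5 years. Hence:
- bias of 5 years minus baseline in returners = (0.8 - 0.5)*s* = 0.3*s*
- bias of 5 years minus 12-15 months in returners = (0.8 - 1)*s* = -0.2*s*

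**Results.** The value of *s* comes from numerical integration. The other columns come from a simulation of 1,000,000 patients.

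| Odds ratio per SD | Return | *s* | 5 y minus baseline, returners (truth -0.50) | Bias | 5 y minus 12-15 mo, returners (truth 0) |
|---|---|---|---|---|---|
| 1.5 | 80% | 0.079 | -0.476 | 0.023 | -0.016 |
| 1.5 | 60% | 0.156 | -0.454 | 0.046 | -0.033 |
| 1.5 | 40% | 0.234 | -0.430 | 0.069 | -0.047 |
| 2 | 80% | 0.129 | -0.460 | 0.039 | -0.026 |
| 2 | 60% | 0.251 | -0.426 | 0.073 | -0.051 |
| 2 | 40% | 0.376 | -0.387 | 0.112 | -0.076 |
| 3 | 80% | 0.186 | -0.443 | 0.056 | -0.037 |
| 3 | 60% | 0.354 | -0.394 | 0.105 | -0.071 |
| 3 | 40% | 0.531 | -0.340 | 0.160 | -0.106 |

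Check on the last row: 0.3 × 0.531 = 0.159 and -0.2 × 0.531 = -0.106, as simulated.

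- At odds ratio 1, *s* = 0 and both biases vanish.
- If patients with low values return more often (odds ratios 1/1.5 to 1/3), *s* changes sign by symmetry. The same sizes then appear as false decline.
- An estimate that uses baseline, 12-15 month and 5-year values of all patients gives a change from 12-15 months to 5 years within 0.001 SD of zero in every row. Missing at random holds here by construction.

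The 10-year visit was not simulated. The same reasoning applies, with the correlations and return rates of that visit.

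**The case against.** The strongest reply is that this is one sentence in a condensed article about an analysis that is openly deferred. Long-term collection runs until at least 2036, the article says the statistics may change, and analysis sets and missing-data handling usually belong to the analysis plan. The named comparison also answers the stated objective, and recovery after the first year is not an objective. Much of this stands, and it limits how far the point goes. Four stronger readings are not supported:

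- **That change after the first year will never be tested.** The article leaves the method open and plans mixed models with unspecified visits. What can be said is that no such contrast is named and that nothing written commits the models to a time effect.
- **That each comparison is fixed as a complete-pair analysis.** The analysis set is not stated. This follows only if the paired tests are carried over.
- **That the platform will join raw visit means into one curve.** Anticipated Findings says that a mean curve alone is not enough and adds individual curves. It does not say how the mean curve is built or which visits it connects.
- **That a within-patient test of 5 years against 12-15 months would cure the problem.** In returners alone it errs the other way, by 0.02 to 0.11 SD in the illustration. If the paired method is carried over, the baseline comparisons are themselves within patients.

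The reply does not remove the core. The article does more than stay silent: it names its long-term comparison, and that comparison omits a measurement already collected. The reservation about adapting the statistics refers to future therapies, not to missing visits, and attrition is answered only by numbers.

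**Conclusion.** The point holds in limited form. The long-term method as written is weaker than an analysis of all visits that needs no new data, and under selective return it gives a biased long-term change.

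In the illustration the bias is 0.02 to 0.16 SD. Relative to the 0.5 SD change this is 0.023/0.5 = about 5% to 0.160/0.5 = 32%. These figures rest on the assumed 0.8 correlation, return rates and odds ratios, and on a paired analysis in returners. By the formula, the bias would shrink to zero if the two correlations were equal or if return were unrelated to the 12-15 month value. The documents do not allow a statement about its actual size or direction.

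The change is worth making before 5-year data arrive. It does not affect the primary short-term analysis.

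**What to change.** In Data Analysis, replace the long-term sentence with the following plan:

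1. Estimate long-term changes per sex and protocol (or per ICD group where protocols are small) from one repeated-measures mixed model with visit as a factor. Use the baseline, 12-15 month, 5-year and 10-year values of all patients, including those who miss a later visit.
2. Keep 5 and 10 years versus baseline as the main long-term result.
3. Add 5 and 10 years versus 12-15 months as exploratory contrasts from the same model, not as paired tests in returners only.
4. Take any long-term mean shown on the platform from this model.
5. State the missing-at-random assumption.

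The cost is some analysis work and reliance on missing at random, which the data cannot verify. No extra visits or data are needed, and mixed models are already part of the plan.

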**Methods:**

First, previously published studies on the gonadotoxicity of chemo- and radiotherapies among patients with cancer will be systematically analyzed. Second, a prospective cohort study set up by approximately 70 centers in Germany, Switzerland, and Austria will collect the following data: ovarian function by analyzing anti-Müllerian hormone (AMH) concentrations and testicular function by analyzing sperm parameters and total testosterone immediately before and around 1 year after gonadotoxic therapies (short-term fertility). A follow-up of these fertility parameters, including history of conceptions, will be performed 5 and 10 years after gonadotoxic therapies (long-term fertility). Additionally, the proportion of patients undergoing fertility-preserving procedures, their satisfaction with these procedures, and the amount of gametes and gonadal tissue and the children achieved by using the frozen material will be analyzed. Third, the data will be merged to create the internet-based data platform FertiTOX. The platform will be structured in accordance with the *ICD* (*International Classification of Diseases*) classification of cancer diseases and will be easily be accessible using a specific App.

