### Study Registry

Data will be collected using the REDCap (Research Electronic Data Capture) software, a secure web application for building databases [16]. The REDCap registry has been set up and optimized by the study consortium with the support of the Clinical Trials Unit in Bern, REDCap technicians, and statisticians. The contents of the study registry (consultation before and 12-15 months after the end of the gonadotoxic therapy) are shown in the paper version of the registry (Multimedia Appendices 2-5). The participating centers will add the data to the registry without adding any definite identifiers such as name and date of birth. The participating centers can only see their patients. Patients can be traced with an individual code that is safeguarded by the centers. Only very few authorized persons will be provided access to all data in order to assess the data quality and to remind the centers to invite the patients for follow-up consultations.

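### The before-after AMH comparison does not separate women who have ovarian tissue removed for freezing, so where the baseline sample precedes removal, any loss from surgery counts as an effect of the cancer therapy

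*Protocol article*

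**What the plan says.** - **End point.** End Points: "The primary end points are the AMH concentration in women and sperm count before and after gonadotoxic treatments". Timing: "End points will be assessed before and 12-15 months after the end of the gonadotoxic treatments".
- **Primary analysis.** Data Analysis: "The impact of cancer therapies and chemotherapies on the primary outcomes will be assessed for each *ICD* cancer group" and for each regimen, by "comparing values measured before and after the gonadotoxic therapy using paired *t* tests". There is no comparison group.
- **Tissue freezing.** The same section lists "freezing of ovarian tissue, oocytes and embryos, testicular tissue, and sperm" as procedures whose frequency is reported with a Wilson interval and examined by logistic regression. This is the only use that section makes of the information.
- **Adjustment.** The one announced stratification is by female age group. The mixed models address "the effects of different cancers, treatment protocols, age, and the presence of the patients" (the sentence goes on to the children that patients already have).
- **Eligibility and limitations.** Inclusion Criteria name age and type of cancer treatment. Neither that section nor Limitations mentions removal of ovarian tissue.
- **Baseline timing.** The abstract's Methods say "immediately before and around 1 year after gonadotoxic therapies (short-term fertility". Study Registry describes the forms by "consultation before and 12-15 months after the end of the gonadotoxic therapy".

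**The concern.** In an uncontrolled before-after comparison, anything that lowers AMH between the two samples becomes part of the estimated effect. One such event is built into this cohort. Patients are recruited at fertility counseling before therapy, and some women will then have ovarian tissue removed for freezing. The article treats AMH as its measure of ovarian reserve, so taking out ovarian tissue plausibly acts on the very quantity that is measured.

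The results are meant to show, regimen by regimen, how gonadotoxic a therapy is, and to be published on an open platform used for counseling. A regimen whose AMH fall is partly surgical would look more toxic than it is. The Objectives plan to study the uptake of fertility preservation in relation to cancer type and treatment protocol, so differing uptake is a possibility that the study itself considers. If uptake does differ, comparisons between regimens are affected as well as the single estimates. A larger sample does not remove such a bias; it only makes the shift more likely to reach significance.

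**Working it through.** **1. Reproduce the plan's own power figures.** Inputs from Sample Size Calculation and Table 1: AMH mean equal to its SD, a 50% fall giving effect size 0.5, intraindividual correlation 0.5, two-sided level 0.0006.

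- Šidák level: 43 groups × 2 sexes = 86 tests; 1 − 0.95^(1/86) = 0.000596, which rounds to 0.0006.
- SD of differences = SD × √(2(1 − 0.5)) = SD. A mean fall expressed as a fraction of the baseline mean is therefore directly the standardized paired effect.
- Exact paired t test power (noncentral t) with n = cases ÷ protocols: bone n = 133, 98.6%; female genital n = 116, 96.5%; mesothelial and soft tissue n = 66, 67.2%; leukemia n = 40, 30.7% (stated 30.6%).

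All female powers in Table 1 reproduce to within 0.1 point, so the same model can be used below.

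**2. Shift from removal alone.** Let p be the share of women with tissue removed between the samples and f the proportional AMH loss from removal. Neither is in the document. Assumed ranges: p = 10-40%, f = 25-50%. With no therapy effect, the mean fall is p × f.

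- Low end: 0.10 × 0.25 = 2.5%.
- Intermediate example: 0.20 × 0.30 = 6%.
- High end: 0.40 × 0.50 = 20%.

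Against the 50% fall for which the study is sized, these are 5%, 12% and 40%.

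**3. Chance that a non-toxic regimen is declared significant.** Paired t test as in step 1, two-sided 0.0006. Sizes: Hodgkin lymphoma 1000 ÷ 2 = 500 per protocol, or 250 women after the 1:1 sex split in the table footnote; breast 2000 ÷ 6 = 333.

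| Mean fall from removal | n = 250 | n = 333 | n = 500 |
|---|---|---|---|
| 2.5% | 0.1% | 0.15% | 0.2% |
| 6% | 0.6% | 0.9% | 1.8% |
| 20% | 38.0% | 57.4% | 84.5% |

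The planned analysis uses false discovery rate adjustment, whose effective threshold depends on the other results and can be looser than 0.0006. The table is then a cautious figure for the chance of significance.

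**4. When the therapy itself is toxic.** If losses multiply (an assumption), removal adds p × f × (1 − therapy loss). With an 80% fall from therapy, the high end adds 0.40 × 0.50 × 0.20 = 4 percentage points instead of 20.

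**5. Order of sampling and removal.** The abstract's wording, read literally, allows a sample taken after tissue removal and just before therapy. The registry wording, tied to the pre-therapy consultation, suggests a sample taken before removal. End Points says only that the value is from before treatment. The order is therefore open. If the sample always follows removal, this mechanism largely disappears.

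**The case against.** The strongest reply has four parts.

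- **No analysis set is defined.** The article does not say that women with tissue removed stay in the comparison, and exclusions may be left to an analysis plan that is not shown. This stands in part. But the article does name its strata and mixed-model terms, and it labels the whole change as the impact of therapy. Followed as written, it has nothing that separates the two effects.
- **The baseline may follow removal.** This stands, and the point is conditional for that reason.
- **The size is assumed, and the large figures sit at one corner of the range.** This stands. At a 6% shift the chance of significance at 0.0006 is at most 1.8% for the sizes above. The distortion of the estimate remains even when no test crosses the threshold.
- **The study is exploratory and sized for a 50% fall.** This is true, but the regimen-specific estimates are what will be published and used.

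A reader might go further and infer that the bias is largest in the most toxic regimens, so that prior belief about toxicity confirms itself. The document does not support this. It gives no uptake by regimen, the figure with the indication algorithm is not shown, and step 4 shows the added fall shrinking where the therapy is strongly toxic. A reader might also extend the point to testicular tissue and sperm count; the document offers no figure or argument for that.

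**Conclusion.** The point holds in conditional form. The plan attributes the whole before-after AMH change to therapy, while a procedure that may itself lower AMH occurs in some of the same women and is used only as a frequency outcome. Where baseline AMH precedes removal, the regimen's estimated effect includes any surgical loss. The assumed ranges give a spurious mean fall of 2.5-20% for a non-toxic regimen, from negligible to material, and less for a strongly toxic one. The result rests on three things that the article does not settle: the order of sampling and removal, the share of women with tissue removed, and the AMH loss that removal causes. It disputes no stated figure; Table 1 was used only to confirm the model.

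**What to change.** 1. Record for each woman whether the baseline AMH sample was taken before or after ovarian tissue removal.
2. Report the AMH change per regimen separately for women with and without ovarian tissue removed between the two samples. Base the regimen's gonadotoxicity estimate on women without removal, and show the all-women result alongside.
3. Add a tissue-removal-by-time term to the linear mixed model, fitted to all women.

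**Cost.** Mostly analysis wording, since the procedure is already to be counted per protocol; the sampling order may need one added registry item. The restricted set loses patients in proportion to the removal share, and that loss need not be small. At a 40% share a mesothelial and soft tissue protocol falls from 66 to about 40 women (66 × 0.60 = 39.6), and its power from 67% to about 31%. Women without removal may also differ from the rest in ways related to AMH. Keeping the all-women model and result guards against both.
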